#### Power and sample size

The sample size of 200 participants will provide power of .80 to detect at least small-to-medium effects (Cohen’s *d* = .40) using two-tailed, between-groups, planned comparisons with an error probability of .05, reflecting the ceiling of statistical power. Given the nature of SUDs and their potential impact on the stability of participants’ lives, we conservatively estimate that 33% will attrit from the study before the primary endpoint of 36 months. This is more conservative than what has been observed in Washington State, where 72% of participants who enrolled in PCAP remained in the program for 36 months. A sample size of 132 participants will provide power of .80 to detect at least medium effects (Cohen’s *d* = .50), reflecting the anticipated floor of statistical power.

### Data and safety monitoring {21a} {21b} {22} {24}

All procedures will be reviewed and approved by the University of Oklahoma IRB with annual reviews. Exclusively using psychosocial methods, the intervention to be evaluated in this study is deemed low risk. Accordingly, an external data and safety monitoring board will not be used. The study PIs ([name]) will be jointly responsible for data and safety monitoring and will meet for this purpose at least semi-annually. Interim analyses will be conducted at least every 6 months. Every week, the investigators review recruitment and retention rates. Semi-annually, they review baseline demographics, adverse events, and primary and secondary outcomes and consider whether there are relatively greater risks in either arm of the trial that warrant stopping the trial. Anticipated potential and reportable adverse events include but are not limited to breaches of confidentiality, death of a subject, reports of acts of violence, child abuse, and complaints about the study or the research team. Per state law, child abuse will be reported to Children’s Protective Services within 48 h, as stated in the consent form. Should an unanticipated adverse event occur, the following steps will be taken: (1) the participant will be informed as to the nature of the event, and its possible implications; (2) the PIs will immediately notify the IRB; (3) the PIs will consult with the Co-Is to review existing safeguards to determine how and why the event occurred; (4) data collection will be halted until new/modified safeguards are developed and implemented; (5) the IRB will review the new procedures, and data collection will resume after a new approval is granted. In addition, the funding agencies will be informed of any actions taken by the IRB at any time as a result of continuing reviews.

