#### Assessment procedures

Whenever feasible, participants will complete study assessments at a private workstation at one of the study sites, connecting with the research coordinator via Zoom videoconferencing. In situations where a participant cannot come to the site, assessments may be conducted with the interview portion via phone and the survey portion completed via web link or on paper forms to be returned via US Mail to the research office. Alerts will be used to remind research staff of data collection intervals. To maintain currency of contact information, research staff will check in with study participants in both groups every 3 months between data collection intervals with a brief online form sent by text message.

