### Frequency and plans for auditing trial {23}

The trial is overseen by a group of investigators and a full-time Project Director at the University of Oklahoma and the University of Washington. A full-time research coordinator is responsible for data collection. This group oversees the implementation and evaluation of PCAP. The direct services are managed by a Supervisory/Manager in OU Outreach’s Southwest Prevention Center (SWPC). The Project Director meets weekly with the research coordinator and the investigator team, along with other meetings as needed. The investigator team and Project Director meet monthly with the SWPC to coordinate activities. The Direct Services team meets weekly with the SWPC Manager. The investigators meet weekly to closely monitor the PCAP trial and discuss the progress of the study and any issues that may arise during its conduct. Given the low-risk nature of the intervention, no external monitoring committee is used. The project also has a Parent Advisory Committee with their own leadership structure who meet quarterly with the full project teams. The Parent Advisory Committee also is invited to monthly investigator team meetings. They have advised on measurement, recruitment, retention, hiring, and direct services. They have also attended conferences and represented PCAP in public forums. We have no plans for an independent monitor.

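### The unblinded investigators who run the trial review accumulating outcomes at least every 6 months and may stop it: this permits operational bias and leaves an unadjusted outcome-based stop open

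*Protocol article*

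**What the plan says.** Under *Data and safety monitoring*, the protocol article states: "Interim analyses will be conducted at least every 6 months". The principal investigators are jointly responsible for this monitoring. At the semi-annual reviews "they review baseline demographics, adverse events, and primary and secondary outcomes and consider whether there are relatively greater risks in either arm", and the question put to them is whether such a difference justifies stopping. That section and *Frequency and plans for auditing trial* rule out an external board and an independent monitor, on the ground that the intervention is low risk. *Blinding* says that participants and staff know the assignment.

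The auditing section also describes who meets whom: "The Project Director meets weekly with the research coordinator and the investigator team". The investigator team and the Project Director meet monthly with the organisation that manages the direct services. The research coordinator conducts the interviews and enters the answers (*Assessment procedures*, *Data management*). The *Discussion* names reliance on self-report, including for substance use, as a limitation.

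*Power and sample size* specifies "two-tailed, between-groups, planned comparisons with an error probability of .05" and does not mention the interim analyses.

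**The concern.** Two things are at stake, and they should be kept apart.

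**Conduct.** Those who see accumulating outcomes by arm are in regular contact with the person who elicits the self-reported outcomes and with the organisation that delivers PCAP. Knowing which arm is ahead can influence how interviews are done, how hard follow-up is pursued and how the programme is delivered. No early stop is needed for this to happen, and results once seen cannot be unseen.

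**Error rate.** The review covers primary and secondary outcomes, and the stopping question concerns either arm. More substance use or more substance-exposed births among controls is the same result as benefit of PCAP. A stop on that ground would be an efficacy stop, made without a stated limit and set against a single .05.

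A smaller point concerns the adverse-event comparison. PCAP participants are to meet a case manager about twice a month, while contact common to both arms is far sparser. Events such as violence or child abuse may therefore come to light more often under PCAP.

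**Working it through.** **1. The plan's own power figures.** Inputs from *Power and sample size*: two-sided .05; "The sample size of 200 participants will provide power of .80 to detect at least small-to-medium effects" (d = .40); "A sample size of 132 participants will provide power of .80 to detect at least medium effects" (d = .50). With equal arms, power is about Φ(d√(n/2) − 1.96), with n per arm.

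- n = 100, d = .40: .40 × √50 = 2.828; Φ(0.868) = .807 (t-test .804).
- n = 66, d = .50: .50 × √33 = 2.872; Φ(0.912) = .819 (t-test .814).

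Both agree with the stated .80, and both assume one final test.

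**2. Number of looks at the primary endpoint (assumed).** *Trial status* gives enrolment from December 2022 to December 2024, and *Study design* makes 36 months the primary endpoint. The 36-month data therefore arrive from about December 2025 to December 2027. Reviews every 6 months over those 24 months give 24/6 = 4 looks. With uniform enrolment these fall at information fractions .25, .50, .75 and 1. The protocol fixes no maximum number of looks.

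**3. Overall error under different stopping rules.** Simulation with 1,000,000 paths of the cumulative z statistic under no true difference:

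| Rule | Error with 4 looks |
|---|---|
| Stop at any look if two-sided p < .05, either direction | .126 two-sided |
| Same rule, false claim of PCAP benefit only (nominal .025) | .064 |
| Interim stop only for harm under PCAP; benefit tested once at the end | about .025 |
| Interim stop at p < .001 (absolute z > 3.29), final test at .05 | .051 two-sided |

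With 6 to 10 equally spaced looks, the last rule stays at .051 to .052. Looking without any possibility of stopping on outcomes leaves the final test's error unchanged.

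**4. Conduct risk.** This follows from the text rather than from arithmetic. Four features occur together: outcome review that is by implication by arm; reviewers who meet weekly with the data collector and monthly with the service organisation; an open-label design; and self-reported outcomes. No independent party stands between the results and the trial's conduct.

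**5. Contacts by arm.** Two planned visits a month for 36 months is 2 × 36 = 72 under PCAP. Research staff will "check in with study participants in both groups every 3 months", between the data collection times. That is about 36/3 = 12 contacts common to both arms, nearer 9 forms plus 3 annual assessments. The form is meant to keep contact details current and is not described as a way to capture events.

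**The case against.** The strongest reply is that the only stated ground for stopping is risk. No efficacy or futility stop is planned, and a harm-only stop does not raise the false-benefit rate. This stands. A reader might infer that the final .05 test is already compromised, but the article does not support that. Inflation needs a rule allowing a stop on outcome differences that favour PCAP, and the article leaves this open without stating it.

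A reader might also count every semi-annual review and reach .176 (8 looks) or .193 (10 looks). Those figures treat all reviews as equally spaced looks at one statistic. Reviews before about December 2025 contain no 36-month data, and *Data analysis plan* compares the arms separately at 12, 24 and 36 months. The 4-look figure is the relevant one for the primary endpoint.

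Third, 72 visits against 12 contacts is not a ratio of detection opportunities. Both arms have annual assessments that cover child protective services and legal involvement, and PCAP participants receive the 3-month form too. Unequal detection is plausible, but its size is unknown.

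Fourth, numerical limits may exist in the full protocol or the analysis plan, and the lack of an external board is disclosed with a reason. Both are fair, and neither is the point here. A limit held elsewhere would not change the stated choice that those running the trial see accumulating outcomes. Nor does the article say that results by arm feed into its quality improvement procedures. The conduct concern rests on the meetings and roles it does describe.

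**Conclusion.** The concern holds on conduct. As written, unblinded investigators in regular contact with data collection and service delivery review accumulating primary and secondary outcomes at least twice a year. Review by arm is an inference, but a sound one, because relative risk cannot be judged otherwise. With self-reported outcomes this allows operational bias whether or not the trial stops; its size cannot be calculated from the article.

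On error control the point is conditional. The false-benefit rate stays at about .025 if only harm under PCAP can stop the trial. It rises to about .064 (.126 two-sided) if each of 4 looks at the 36-month endpoint could stop it at p < .05 in either direction. The number and spacing of looks are assumptions, and stops based on 12- or 24-month data are not covered by these figures. What needs correcting is that the article does not say whether an outcome difference can stop the trial. Unequal adverse-event detection is a secondary point.

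**What to change.** - Limit the semi-annual by-arm review to deaths and adverse events. Review primary and secondary outcomes only pooled over arms, for completeness and data quality, until the last 36-month visit.
- If an outcome-based stop is wanted, say so and state a Haybittle-Peto limit: p < .001 at each interim and .05 at the end, for an overall error of about .051 to .052. The final critical value is unchanged, so the power statement stands. This limit controls error but not operational bias, so under this option the by-arm outcome results should be reviewed by someone outside the trial's conduct.
- Base between-arm adverse-event comparisons on routes common to both arms, such as the annual assessments, and list events detected by case managers separately.

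The first and third changes are a matter of protocol and IRB wording and need no extra staff. The investigators give up early sight of outcome results by arm. The optional outcome-based stop would also need an independent reviewer's time.

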### Poor outcomes from perinatal substance use

Perinatal substance use can have significant adverse effects on maternal and child health. Drug overdose is now a leading cause of death during and shortly after pregnancy. Overdose deaths among pregnant and postpartum individuals increased by 81% from 2017 to 2020 [9], and up to 22% of pregnancy-associated deaths are attributable to substance use [10]. Substance use during pregnancy is linked to decreased prenatal and postpartum care access [11], and the use of opioids or illicit stimulants during pregnancy is associated with a fourfold increase in risk of postpartum readmission [2]. Women with SUDs have a 6.2-fold increased risk of postpartum suicide attempts, and the risk nearly doubles for those with both SUD and psychiatric diagnoses [12].

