### Description of the intervention {11a} {11b} {11d}

The Parent–Child Assistance Program (PCAP) has been described in detail elsewhere [25, 28]. In brief, PCAP is a 3-year intervention for pregnant and post-partum individuals with problematic or at-risk substance use during their most recent pregnancy. Built on the theoretical foundations of relational theory [29], the transtheoretical model of behavior change [30], and harm reduction [31], PCAP aims to support birthing individuals in completing SUD treatment and link them with comprehensive community resources to help them stay in recovery, build healthy lives, and avoid exposing any future children to alcohol or drugs prenatally. PCAP provides program participants with a bachelor’s-level case manager (CM), with whom they meet approximately bi-weekly, in participants’ own homes or elsewhere in the community. CMs typically work with up to 20 participants and their families, serve as role models, help them to articulate their own goals and take steps to reach them, and provide transportation and practical assistance when needed in support of participants’ goals. The intervention manual is available at https://pcapwa.org/manual. There are no formal criteria for modifying the intervention for a given participant. The design of the intervention provides for flexibility to adjust the frequency of contacts according to the participant’s needs and preferences while aiming for an average of two face-to-face contacts per month over the course of the intervention. Consistent with the intent-to-treat approach, participants who ask to suspend their participation in the intervention or withdraw from the intervention completely will remain in the study unless they specifically ask to withdraw from the study as a whole.

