#### Fidelity monitoring

Fidelity to the PCAP model will be monitored by examining time logs for CMs and monthly and semi-annual reports of participant status. CMs will record the amount of time spent working directly with or on behalf of each participant, including face-to-face meetings, time spent transporting the participant, phone communication with the participant, and other time spent working on a participant’s case without the participant present, such as working with an agency on behalf of the participant, time spent with participant’s family, and time spent corresponding with the participant. Specifically, we will monitor the number of visits per month, maintaining an expectation that CMs meet with each intervention participant twice per month and that CMs spend at least 55% of their time working with or on behalf of intervention participants. A case management supervisor will monitor time spent with participants and intervention milestones, providing feedback when deviations from fidelity are noted.

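### The semi-annual stopping review compares adverse events between arms, but PCAP participants are seen far more often than controls, so that part of the comparison is likely tilted toward apparent PCAP harm

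*Protocol article*

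**What the plan says.** Under Data and safety monitoring, the principal investigators carry out the review without an external board: "Semi-annually, they review baseline demographics, adverse events, and primary and secondary outcomes". From that material they "consider whether there are relatively greater risks in either arm of the trial that warrant stopping the trial". The reportable events, given as an open list, include breaches of confidentiality and "death of a subject, reports of acts of violence, child abuse, and complaints about the study or the research team".

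Contact differs by arm:

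- **PCAP arm.** Description of the intervention has case managers "aiming for an average of two face-to-face contacts per month over the course of the intervention". Fidelity monitoring repeats this as "an expectation that CMs meet with each intervention participant twice per month" and adds "monthly and semi-annual reports of participant status". Under Intervention adherence, case managers reach out proactively and obtain consent to contact a friend or relative if the participant cannot be found. Under Frequency and plans for auditing trial, the direct services team meets its manager weekly, and the investigators meet the direct services centre monthly.
- **Both arms.** Study design sets assessments at baseline and at 12, 24 and 36 months. Assessment procedures adds a brief form sent by text: "To maintain currency of contact information, research staff will check in with study participants in both groups every 3 months".
- **Control arm.** Description of the control condition provides a list of local services and no case manager.

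Under Blinding, assignment is known to participants and staff once made.

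**The concern.** The article makes relative risk between arms a ground for stopping, and one input is a set of events that staff mostly learn of through contact. One arm has frequent contact and a standing route by which its events reach the investigators. The other has a text form with a different stated purpose and one interview a year. Unequal recording is then built into the schedule and can occur even when the true risks are equal.

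The review could be misled in two ways. It could see an excess in PCAP that reflects closer observation, or it could miss events in controls and so fail to see a benefit of PCAP. As the review is unblinded and has neither an external board nor an independent monitor, the investigators themselves would have to recognise the artefact.

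**Working it through.** The plan gives no figure for adverse-event ascertainment, so there is nothing of its own to reproduce. The check has two parts: contact counts, which follow from the text, and an illustration, which rests on assumptions.

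**1. Scheduled contacts per participant**

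Inputs: two case-manager meetings a month (Description of the intervention; Fidelity monitoring), three post-baseline assessments (Study design), and texts every three months between assessments, read here as months 3, 6 and 9 of each year (Assessment procedures).

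| | PCAP | Control |
|---|---|---|
| Case-manager meetings, 36 months | 2 × 36 = 72 | 0 |
| Text forms, 36 months | 3 × 3 = 9 | 9 |
| Annual assessments | 3 | 3 |
| Total, 36 months | 84 | 12 |
| Case-manager meetings per 6-month interval | 2 × 6 = 12 | 0 |

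The ratio of totals is 84 / 12 = 7. A control has an interview in only 3 of the 6 six-month intervals; in the others the only scheduled contact is the text form. These counts assume full delivery. At half delivery a PCAP participant would still have 12 / 2 = 6 case-manager meetings per interval against none.

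**2. From contact to apparent risk**

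Let p be the true risk in both arms, and let dT and dC be the proportions of events detected in PCAP and control. The recorded risks are p × dT and p × dC, so the apparent risk ratio is dT / dC whatever p is. It exceeds 1 whenever detection is higher in PCAP.

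Assumptions, none of them in the documents: 100 per arm, p from 10% to 30%, dT = 90%, dC varied. The last column is the probability that a two-sided Fisher test at .05 shows PCAP as worse, from exact binomial calculation.

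| dC | Apparent ratio | Recorded events per 100 at p = 30% | PCAP falsely worse, p = 10% to 30% |
|---|---|---|---|
| 90% | 1.0 | 27 v 27 | 1.4% to 1.7% |
| 70% | 1.29 | 27 v 21 | 4.5% to 12.8% |
| 50% | 1.8 | 27 v 15 | 13% to 48.5% |
| 30% | 3.0 | 27 v 9 | 32.6% to 90% |

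Three cases by the pooled z-test:

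- 27 v 15: pooled 0.21, SE = √(0.21 × 0.79 × 2/100) = 0.0576, z = 0.12 / 0.0576 = 2.08, p = .037.
- 27 v 21: pooled 0.24, SE = √(0.24 × 0.76 × 2/100) = 0.0604, z = 0.06 / 0.0604 = 0.99, p about .32.
- 9 v 5 (p = 10%, dC = 50%): pooled 0.07, SE = √(0.07 × 0.93 × 2/100) = 0.0361, z = 0.04 / 0.0361 = 1.1, p about .27.

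The reverse error has the same arithmetic. With dC = 70%, a true risk ratio of 70 / 90 = 0.78 in favour of PCAP would be recorded as 1.0.

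These are 36-month totals; early reviews would have fewer events. The plan sets no significance test for adverse events, so the tests only gauge how large the artefact could look.

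**The case against.** The strongest reply is that the article does not say how adverse events are elicited in either arm. A fuller protocol and the study guides exist but are not shown, and they may contain a symmetric procedure. This stands as a limit on certainty. It does not remove the point, which sets a stated between-arm criterion beside a stated, unequal contact schedule.

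Other parts of the reply stand:

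- **The whole stopping review is not compromised.** A reader might infer that it is. But the review also uses primary and secondary outcomes, collected with the same instruments on the same schedule in both arms.
- **Control events are not all lost.** Follow-up interviews cover legal involvement, psychiatric disorders and child custody, the added items include child protective services involvement, and the survey covers criminal justice involvement. Some events in controls will surface, though often after the review for which they were relevant.
- **Overdose and suicide attempt are not shown to be excluded.** The background stresses such risks ("Women with SUDs have a 6.2-fold increased risk of postpartum suicide attempts"), and neither is a named event. A reader might conclude that they would be seen in one arm only. The list is expressly open, however, and the item content of the interviews is not shown.
- **Case managers are not named as the reporters of child abuse.** The duty is stated generally. A reader might infer that their reports bias the custody and foster-care outcomes. The text does not establish this, and an effect of having a case manager is arguably part of what intent-to-treat estimates.
- **The 7-fold ratio counts contacts, not detected events.** Delivery may also fall short: Power and sample size cites 72% programme retention at 36 months in Washington State.

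Finally, stopping is a judgement by investigators who know how the arms differ. That lowers the chance of a mistaken decision, but it does not give them comparable counts.

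**Conclusion.** The concern holds for the adverse-event part of the stopping review. Followed as written, the schedule makes that comparison likely to lean toward apparent PCAP harm and to under-count events in controls. The direction rests on one assumption, that more frequent contact brings more events to light, which is reasonable for violence, child abuse and complaints, and probably for deaths too.

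The size is unknown. Across the assumed control detection rates the apparent ratio runs from 1.29 to 3.0, and at 70% detection the distortion would usually not reach conventional significance. The documents do not support saying that a false stopping signal is probable, or that the trial has no valid comparison of harm. The defect is moderate and can be put right cheaply while follow-up continues: with enrolment expected to run to December 2024, 36-month follow-up extends to about December 2027.

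**What to change.** - Ask the same short, fixed set of safety items in both arms at the same times: at the annual assessments and, where privacy and mandatory reporting allow, on the existing three-monthly check-in.
- Add a field in REDCap for the source of every event (participant report on the common items, case manager, other).
- Base the main between-arm adverse-event comparison on events captured the same way in both arms.
- Show case-manager-detected events beside it, tabulated by source. Dropping them could hide a real harm of the intervention.
- Leave individual reporting to the IRB and the authorities unchanged.

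The cost is a few items on existing forms, one database field and a submission to the IRB, the route that Protocol amendments already gives for changes to data collection forms. The downsides are slight participant burden, fewer events in the main comparison, and uneven capture of events before the change, which should be stated when the comparison is reported. Self-report of violence or abuse by text needs care over privacy and reporting duties; if that cannot be settled, the items should be confined to the annual assessments, and the lag at each semi-annual review acknowledged.
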